#### Secondary:

- To assess difference in the survival of the patients in both the groups during hospitalization.

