| **Inclusion Criteria** | - Stage 1 and 2 (Staging document annexed) of ROCM - Age > 18 years - All genders - Fungal smear analysis through KOH staining/ microscopy of affected area showing presence of mucormycetes (to save precious time), followed by following exploratory imaging techniques:   - CEMRI (for ruling out Stages 3 and 4)   - CT-guided endoscopy-cum-biopsy (for detailed histopathology study) |
| **Exclusion Criteria** | - ROCM cases in stages 3 and 4(Staging document annexed) presenting with bony erosion, cerebral vascular invasion, invasion into the cranium, orbital apex or cribriform plate of the ethmoid bone, cavernous sinus (II-VI cranial nerve palsies) will be excluded. - Diagnosed cases of Pulmonary ,Cutaneous, Gastrointestinal ,Advanced, disseminated mucormycosis will be excluded. - Pregnant and lactating women. - In the opinion of the clinical team, progression to death is imminent and inevitable within the next 24 hours, irrespective of the provision of treatments. |
| **Follow-up period** | - Patient will be assessed clinically twice a day; MRI/endoscopy-cum-biopsy will be assessed on day 1, 14 and 28. |
| **Outcomes** | **Primary Outcome**   1. Change in condition as seen in standard imaging or other diagnostic techniques:  - MRI contrast in ROCM cases   **Secondary Outcomes**   1. To assess difference in the survival of the patients in both the groups during hospitalization. |
| **Endpoint** | - Recovery as per the outcome parameters, followed by discharge from hospital - Advanced, disseminated mucormycosis - Death of the patient |
| **Study Product, Dose, Route** | - Individualized homoeopathic medicine in appropriate dose, orally, four times daily; or more frequently in severe cases. |
| Placebo | Placebo group patients will receive identical placebo (globules moistened with dispensing alcohol) as an add on to standard protocol treatment. Dose repetition will be a in similar pattern to medicine group. |
| Duration of administration | Maximum 28 days (depending on the patient’s admission duration) |
| Statistical Methodology | All primary efficacy analyses will be conducted in the Intention-to-treat (ITT) population; thus, all randomized patients should be included in the primary analysis. |
| Funding Agency | Central Council for Research in Homoeopathy, Ministry of AYUSH, Govt. of India |
| Budget | Rs. 75 lakhs approx. |

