### Duration of intervention:

28 days. However, if patient is discharged before, the medicines will continue, if needed, and the follow up will be done telephonically on the 14^th^ and 28^th^ day of illness.

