## LABORATORY INVESTIGATIONS

| **INVESTIGATIONS** | | |
| --- | --- | --- |
| - **Lab parameters** | CBC, ESR, FBS, PPBS, HbA1C, LFT, KFT with electrolytes | D0 and as per IMP |
| - **Imaging technique** | - CEMRI of Brain with orbits and sinuses. | - (Only at inclusion) |
|  | - CEMRI PNS | - D0 (or latest report if it is within 03 days of enrolment day), D14 and D28, or before or after as per IMP/ requirement |
|  | - CT guided endoscopy-cum-biopsy Fungal smear/KOH staining | - As per IMP, if required |

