**Statistical analysis:**

Data collected will be compiled on to a MS Office excel worksheet & will be subjected to statistical analysis using an appropriate package like SPSS software. Descriptive statistics like frequency (n) & percentage (%) of categorical data, mean & Standard deviation of numerical data in each group / subgroup will be depicted.

Frequency (n) & percentage (%) of various categories in each group / subgroup will be compared using chi square test.

Normality of numerical data will be checked using Shapiro – Wilk test or Kolmogorov-Smirnov test. Depending on the normality of data, statistical tests will be determined.

For a numerical continuous data following a normal distribution, inter group comparison (2 groups) will be done using t test, else a non parametric substitute like Mann Whitney U test will be used.

Intra group comparisons for a numerical continuous data following a normal distribution will be done using paired t test (for 2 observations) or repeated measures ANOVA for >2 observations, else a non parametric substitute like Wilcoxon signed rank test (for 2 observations) or Friedman’s test for >2 observations will be used.

Frequency (n) & percentage (%) of various responses in each time interval will be compared using chi square test / McNemar’s test.

Keeping alpha error at 5% and Beta error at 20%, power at 80%, p<0.05 will be considered statistically significant.

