## STATISTICAL METHODS

Data analysis will be done through Intention To Treat (ITT) method, thus, all randomized patients should be included in the primary analysis. Additional analyses (e.g. subgroup analysis as per age, sex, perceived risk categories will also be carried out. Statistical advice will be sought before initiation. Kolmogorov-Smirnov tests will be used to analyse the normality of the data distribution. Data will be presented in number, percentage, Mean with 95% Confidence Interval, SD, Median, IQR. Statistical significance will be considered as the p value<0.05. Correlations between individual diagnoses/symptoms/ characteristics will be calculated in a Spearman rank correlation table. Correlations between groups of symptoms will be explored by principal component analysis (PCA). Comparison of baseline characteristics and outcome among all participants will be done by using parametric or non-parametric test. For categorical data χ2 exact test will be used. Concordance of the different methods for appraising result will be measured by Cohen’s kappa and Spearman rank correlation.

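### Survival is compared only up to discharge, with no fixed day, so the time over which a death counts varies between patients and depends on recovery

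*Protocol*

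**What the plan says.** - **Outcome.** Protocol section 3.6 (Secondary) and the synopsis both give the sole secondary outcome as "To assess difference in the survival of the patients in both the groups during hospitalization". Neither gives a day or a time origin.
- **Discharge.** The first endpoint in the synopsis is "Recovery as per the outcome parameters, followed by discharge from hospital". The same row also lists the patient's death, without restricting it to hospital.
- **Treatment duration.** The synopsis has "Maximum 28 days (depending on the patient’s admission duration", so exposure too follows length of stay.
- **After discharge.** Section 3.4 (Duration of intervention) provides two telephone contacts for a patient who leaves before 28 days. Both are timed by "day of illness": one at 14, the other at 28. Calls are planned only for patients who leave early.
- **Imaging clock.** The Laboratory Investigations table schedules contrast MRI of the paranasal sinuses at "D0 (or latest report if it is within 03 days of enrolment day), D14 and D28", with leeway to scan earlier or later.
- **Withdrawal.** Section 3.5 withdraws patients whose disease spreads beyond the eligible range, who need ventilation, or who are unwilling or non-compliant. It does not say whether their vital status is still collected.

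Nowhere does the protocol say that a death learned of by telephone counts in the survival comparison.

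**The concern.** A mortality comparison needs the same period at risk for everyone. Here the period ends at discharge, and discharge follows recovery, which the treatment is meant to improve. Patients who stay longer are watched longer. A patient who dies at home on Day 20 is not a death for this outcome, although the secondary objective concerns the survival of patients admitted with the disease and is not confined to the stay.

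At stake is the trial's only between-arm comparison of mortality. If length of stay were to differ by arm, the arm that discharges earlier would show fewer in-hospital deaths with no effect on death itself. The post-discharge calls might have closed the gap, but as worded they run on a different clock from the rest of the schedule.

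**Working it through.** The protocol gives no mortality rate, length of stay or power calculation for survival, so there is no figure of its own to reproduce. The check has two parts.

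**1. The two clocks.** If the 28th day is counted from illness and a patient enrols on illness day *e*, the last call falls on trial day 28 − *e* and the first on trial day 14 − *e*. The values of *e* are assumed.

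| Illness day at enrolment | First call, trial day | Last call, trial day |
| --- | --- | --- |
| 5 | 9 | 23 |
| 10 | 4 | 18 |
| 14 | 0 | 14 |
| 15 | −1 (before enrolment) | 13 |
| 20 | −6 (before enrolment) | 8 |

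So, read literally, the calls give no common Day 28 status. The protocol also does not say whether the illness is COVID-19 or mucormycosis.

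**2. Size of the distortion.** Assumptions, none from the documents: a constant death hazard, identical in both arms and unchanged by discharge; 28-day mortality *m* from 10% to 40%; every patient discharged at day 14 in one arm and day 21 in the other. The risk of dying before discharge on day *d* is 1 − (1 − *m*)^(*d*/28).

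For *m* = 10%: 1 − 0.90^0.5 = 5.1% and 1 − 0.90^0.75 = 7.6%. For *m* = 40%: 1 − 0.60^0.5 = 22.5% and 1 − 0.60^0.75 = 31.8%.

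| 28-day mortality, both arms | Discharge day 14 | Discharge day 21 | Difference (points) | Risk ratio | Share of 28-day deaths missed (day 14 / day 21) |
| --- | --- | --- | --- | --- | --- |
| 10% | 5.1% | 7.6% | 2.5 | 0.68 | 49% / 24% |
| 20% | 10.6% | 15.4% | 4.9 | 0.69 | 47% / 23% |
| 30% | 16.3% | 23.5% | 7.1 | 0.70 | 46% / 22% |
| 40% | 22.5% | 31.8% | 9.3 | 0.71 | 44% / 20% |

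(Differences are taken before rounding.) With a window fixed at Day 28, both arms have risk *m* and the expected difference is zero.

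The equal hazard after discharge is the assumption that matters most. Since discharge follows recovery, the hazard probably falls, and both the distortion and the missed share shrink. At the limit, where nobody dies between discharge and Day 28, in-hospital death and death by Day 28 coincide and nothing is lost.

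**The case against.** **In-hospital survival is a recognisable choice for an inpatient trial, and this is a secondary outcome.** True, and it bears on how serious the point is. It does not answer the unequal window.

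**The numerical effect is modest at this size.** With 36 per arm, the standard error of the difference is √[p₁(1 − p₁)/36 + p₂(1 − p₂)/36]. That is 5.7 points for 5.1% versus 7.6%, and 10.4 points for 22.5% versus 31.8%. The illustrated distortions of 2.5 and 9.3 points are each below one standard error. This stands. But the distortion is systematic and would, under the trial's own hypothesis, favour the experimental arm.

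**A reader might infer that the window is known to differ between arms.** The protocol does not say so. Under 1:1 randomisation with placebo, it requires the treatment, or discharge decisions, to change length of stay. Only the variation between patients follows directly from the text.

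**A reader might infer that post-discharge deaths go uncollected, or that the call is always the last contact.** Neither is supported. Death is listed as an endpoint with no hospital limit, and the D28 scan, from which discharged patients are not exempted, is a nominal contact on the study clock. Such deaths are outside the named comparison, not necessarily outside the data.

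**The timing of the calls may be loose wording for study day.** Quite possibly: the numbers 14 and 28 match the imaging schedule, and a call before enrolment makes no sense. The two passages still need reconciling.

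**The statistical analysis plan could settle it.** Only in part. It can choose a method, but it cannot supply vital status that was not collected. Censoring at discharge would not help either, because it treats discharged patients as having the same risk as those still admitted. Intention-to-treat analysis keeps patients in the denominator without equalising follow-up.

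A reader might also see a conflict in how the two statistical sections name the test for categorical data. That is ordinary analysis-plan detail and no part of this point.

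**Conclusion.** The concern holds in this form: survival is compared over a window with no fixed day, closed by an outcome-dependent event, and the calls as worded do not restore a common endpoint. Variation between patients, and the exclusion of post-discharge deaths from the comparison, follow from the text. Bias between arms is conditional on length of stay differing by arm.

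The risk ratio of about 0.7 shows direction and possible size only. It rests on an assumed constant and equal hazard and on assumed discharge days, and it overstates the distortion if risk falls after discharge. The change should be made, because this is the only comparison of mortality, but it does not touch the primary outcome.

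**What to change.** - Define the secondary outcome as all-cause death by Day 28 after randomisation, in all randomised patients, whether in hospital or not.
- Time the two planned calls to study Day 14 and study Day 28, so that they share a clock with the imaging.
- Collect Day 28 vital status, at the D28 imaging visit or by call, for every patient, including those withdrawn under section 3.5.
- Keep in-hospital death as a descriptive result.

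The cost is small but more than rewording. Calls are at present planned only for patients discharged early, so some additional vital-status calls are needed for withdrawn patients.

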## LABORATORY INVESTIGATIONS

| **INVESTIGATIONS** | | |
| --- | --- | --- |
| - **Lab parameters** | CBC, ESR, FBS, PPBS, HbA1C, LFT, KFT with electrolytes | D0 and as per IMP |
| - **Imaging technique** | - CEMRI of Brain with orbits and sinuses. | - (Only at inclusion) |
|  | - CEMRI PNS | - D0 (or latest report if it is within 03 days of enrolment day), D14 and D28, or before or after as per IMP/ requirement |
|  | - CT guided endoscopy-cum-biopsy Fungal smear/KOH staining | - As per IMP, if required |

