The management of fungal infection includes administration of antifungal therapeutics with and without surgical interventions.^[[55]](#endnote-55)^ Surgery is necessary due to the massive amount of tissue necrosis occurring during mucormycosis, which may not be prevented by killing the organism.^[[56]](#endnote-56)^ In rhinocerebral mucormycosis, early surgical excision of the infected sinuses and appropriate debridement of the retroorbital space can often prevent the infection from extending into the eye^[[57]](#endnote-57)^, There is growing scientific reports on immune response of antifungal medication but still a large number of studies are not clinical based. Here, in case of fungal infection host response involves both cellular and humoral immunity. However, humoral immunity plays a larger role in offering protection against fungal infection. It has been also reported that cellular immunity associated with Th1-type offer a protectiveresponses against fungal infection via secreting IFN-y. On the contrary, the response of Th2 via IL4 and IL10 triggers and facilitate fungal infection and pathological outcomes. Further, mononuclear immune cells start infiltration at the site of infection and offering a delayed immune activity favoring fungal infections.^[[58]](#endnote-58)^ The poor immune surveillance and cellular immune activity was reported during chronic inflammatory diseases including diabetes and cancer.^[[59]](#endnote-59)^

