### Details of intervention:

A detailed history and examination will be gathered from the already available information of the patient in the admission records at hospital. The patients randomised into experimental group will be interrogated by the homoeopathic physician only for the additional information required from Homoeopathy perspective.

As per each case, individualized homoeopathic medicine will be prescribed. Symptomatic Homoeopathy management of Suspected and Diagnosed cases of Mucormycosis has been advised in Guidelines by Ministry of AYUSH.^[[69]](#endnote-69)^ These guidelines will play a vital role in identification of the indicated medicines in this proposed study.

Daily recording of the administered dose will be recorded and also captured in the Case Record Form (CRF) developed by the Homoeopathy team, which will be having content other than, and in addition to the standard form, which will be filled at the hospital. If there is any change in dosage / prescription of medications during the study period, that will be mentioned with reason in the prescription chart. If these medicines are stopped, that too would be recorded with reason.

The patients assigned to the placebo group will be given placebo in the form of similar looking homoeopathic pills of 30 size, dispensed with the 30% V/V dispensing alcohol.

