### Change of prescription

The prescribed medicine will be changed if no change in the next scheduled laboratory investigations or patient reports to be clinically unwell, even after at least 3 doses of the prescribed medicine.

**In either arm, no patient will be devoid of the conventional management as per IMP at any given point of time**. The allopathic medicines given during the study duration will be recorded specifically, with details of reason for administration, the name of the medicine with dose, along with any other relevant details, in the daily medication sheet as well as the CRF. The participants of the allopathy arm will get non-medicated, similar looking lactose globules, as placebos.

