## 3.6 OUTCOMES

#### Primary:

Change in condition as seen in standard imaging or other diagnostic techniques:

- MRI contrast in ROCM cases

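### The baseline MRI may predate debridement of the sinuses, and the protocol does not ask for surgery to be recorded, so surgery done before randomisation can count as on-study improvement

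*Protocol*

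**What the plan says.** Section 3.6 of the protocol (Outcomes, Primary) defines the primary outcome as "Change in condition as seen in standard imaging or other diagnostic techniques", specified as contrast MRI.

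The Laboratory Investigations table times the repeated scan, contrast-enhanced MRI of the paranasal sinuses, as "D0 (or latest report if it is within 03 days of enrolment day), D14 and D28, or before or after as per IMP/ requirement". No condition refers to an operation. A separate row lists MRI of brain, orbits and sinuses at inclusion only.

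The Background states that "Surgery is necessary due to the massive amount of tissue necrosis occurring during mucormycosis" and describes "early surgical excision of the infected sinuses and appropriate debridement of the retroorbital space". The sinuses are the region that the repeated scan images. Only stages 1 and 2 are enrolled, and Annexure 1 defines stage 2 as sinus involvement.

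Section 3.4 (Change of prescription) says that "no patient will be devoid of the conventional management as per IMP at any given point of time"; what that management contains, surgery included, is not given. On recording, it says "The allopathic medicines given during the study duration will be recorded specifically, with details of reason for administration", followed by name and dose. Details of intervention mentions a homoeopathy case record form with content "in addition to the standard form, which will be filled at the hospital"; the content of that hospital form is not shown.

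The Statistical analysis section plans between-group tests and also within-group before/after tests (paired t test, repeated measures ANOVA, McNemar and non-parametric counterparts).

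**The concern.** A change score attributes to the trial period everything that happens between the baseline scan and the follow-up scan. If the baseline may be up to 3 days old, and the sinuses may be debrided in those days, the score includes tissue removed before the patient was randomised. Two patients with the same clinical course can then score differently only because of scan timing.

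Three things are at stake. The between-arm comparison loses some precision. The within-group tests cannot tell study treatment from surgery. And without a trial record of debridement dates, nobody can readily check whether surgery after randomisation differed between arms. That check matters because the design is described only as single blind: the protocol does not say whether surgeons or MRI readers know the allocation.

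**Working it through.** **Inputs from the protocol.** 36 per arm (synopsis); planned difference 0.10 (Target Sample Size); baseline window of 3 days (Laboratory Investigations). I take D0 as the day of enrolment and randomisation.

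**Assumed inputs, because the documents give none.** Share of patients debrided between baseline scan and follow-up, s = 0.3 to 0.7. Rise in the chance of MRI improvement due to debridement, g = 0.2 to 0.5. Overall improvement rate about 50%. Note that s counts all surgery after the baseline scan. The part that falls before randomisation, which the 3-day window adds, is smaller by an unknown amount.

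**The plan's own figure.** (1.96 + 0.84)² × 0.09 / 0.10² = 7.84 × 0.09 / 0.01 = 70.56, so the stated 71 reproduces. That the text calls this a per-group number while 36 per arm are enrolled is a separate matter. Only the 10-point difference and the 36 are used here.

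**Step 1: can the rule fold earlier surgery into the score?** Patient A is scanned 3 days before enrolment, debrided 1 day before, and has no newer scan. The old report is a valid baseline, so the D14 scan shows cleared sinuses and reads as improvement. Patient B is debrided first and scanned afterwards; the same course shows little change. Both follow the table as written.

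**Step 2: is surgery a required trial record?** Section 3.4 requires conventional medicines and homoeopathic doses to be recorded. Data Collection Methods lists a case record form, a database of physician observations, laboratory reports and homoeopathy data. None of these names a procedure, its date or its extent.

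**Step 3: chance imbalance between arms.** SD of the difference in operated share = √(2s(1−s)/36).
- s = 0.3 or 0.7: √(0.42/36) = 0.108; 95% limits ±0.212.
- s = 0.5: √(0.50/36) = 0.118; 95% limits ±0.231.

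The exact binomial chance of an imbalance of 10 points or more is 37% (s = 0.3 or 0.7) or 41% (s = 0.5). Multiplied by g, one SD moves the between-arm difference by 0.108 × 0.2 = 2 points to 0.118 × 0.5 = 6 points. The 95% limits move it by 0.212 × 0.2 = 4 points to 0.231 × 0.5 = 12 points.

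**Step 4: how much of the standard error is that?** At 50% improvement the outcome variance is 0.25, and the ordinary 95% half-width is 1.96 × √(2 × 0.25/36) = 0.231. With s = 0.5, surgery contributes g² × 0.25:
- g = 0.2: 0.010, or 4% of 0.25. Perfect adjustment cuts the standard error by 1 − √0.96 = 2%.
- g = 0.5: 0.0625, or 25% of 0.25. The cut is 1 − √0.75 = 13%.

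The half-width would go from 23.1 points to between 22.6 and 20.0.

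**Step 5: within-group tests.** Here nothing cancels. The improvement rate in each arm shifts by s × g, from 0.3 × 0.2 = 6 points to 0.7 × 0.5 = 35 points, whatever the study medicine does.

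**The case against.** The strongest reply is that the comparison is randomised. Debridement done before allocation falls on both arms alike in expectation. The 4 to 12 points in Step 3 are sampling variation already inside the standard error, not bias, and setting them against the 10-point planned difference makes ordinary noise look worse than it is. This stands. A reader might infer that the trial cannot separate an adjuvant effect from debridement; for the between-arm comparison the documents do not support that.

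Second, the protocol does not say that medicines are the only thing recorded. A hospital form exists, and these are inpatients. So a reader should not infer that the effect of surgery can never be removed: a date could probably be retrieved. What remains is that the protocol does not require it as trial data.

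Third, the table says the latest report, so a post-operative scan within the window would replace a pre-operative one, and a further scan is listed at inclusion. This narrows the problem to patients with no newer sinus scan. It does not close it, because the inclusion scan is not named as the baseline and is not tied to surgery either.

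Fourth, surgery after randomisation is part of standard care in both arms, and comparing outcomes whatever care is given is a legitimate question for an add-on trial. True. A difference in surgery between arms is possible but not shown. The reason to record it is to be able to look.

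Fifth, covariate adjustment can sit in an SAP that is not at hand. Also true, but an SAP cannot adjust for dates that nobody was asked to collect, and what counts as baseline is a protocol rule.

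**Conclusion.** The point holds as a defect in the baseline rule and in what is recorded. As written, debridement before randomisation can be scored as on-study improvement. The cost is modest for the randomised comparison: at most about a 13% inflation-free gain in standard error is available under the assumed ranges, and less for the pre-randomisation part alone. The cost is serious for the within-group tests, which cannot be interpreted as a treatment effect when surgery falls between the scans.

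Two further readings are tempting and unsupported. One is that debridement is the main driver of the outcome: the Background is general, says management may go with or without surgery, and gives no rate for stages 1 and 2. The other is that the 3-day window is the whole cause: a D0 scan can also precede surgery done later, so tightening the window settles only the part before randomisation. All sizes rest on assumed surgery rates and effects.

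**What to change.** 1. In Laboratory Investigations, accept an earlier MRI report as baseline only if no debridement took place between that scan and randomisation. Otherwise use the D0 scan already in the schedule.
2. In section 3.4 (Change of prescription), require the case record form to hold the date and extent of each debridement in both arms, copied from the hospital record.
3. Adjust the primary between-arm comparison for debridement before randomisation (yes/no), and report debridement after randomisation by arm descriptively.

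Stratifying the allocation list by earlier debridement is optional at this sample size.

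Cost: one sentence in the table, one case record form field, and one covariate. A few patients will not be able to reuse a pre-operative scan. Nothing here changes whether or when surgery is done.
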